## Abstract

**Aim:**

The aim of this study was to test the feasibility and fidelity of an intervention, Moving On, aimed to increase outcome expectations OEs (i.e. what one expects to obtain or avoid as a result of a behaviour) and exercise among breast cancer survivors.

**Design:**

Randomized controlled trial

**Methods:**

Intervention arm participants will be given a theory‐guided booklet that was co‐created by the research team and three physically active breast cancer survivors who exercise to manage late and long‐term treatment effects. Attention control arm participants will be given a similar booklet focused on diet. Participants will have 1 week to complete reading, writing and reflecting activities in the booklets. Study outcomes will be measured through online surveys; exercise will also be measured objectively with a Fitbit^®^. Four weeks postintervention, participants’ thoughts about the usefulness, strengths and weakness of the intervention booklet will be assessed. OEs and exercise will be measured at baseline, 4‐, 8‐ and 12‐week postintervention.

## INTRODUCTION

1

Breast cancer is the most prevalent cancer among women in 145 countries (World Health Organization, 2011). Due to successful treatments for these patients, there are an estimated five million breast cancer survivors worldwide (World Health Organization, 2011). Unfortunately, many survivors experience late and long‐term effects, sometimes as long as 10 years after the completion of the treatment (Kenyon, Mayer, & Owens, 2014). Many of these effects may be decreased by exercise. For example, exercise has been shown to improve body image, self‐esteem, emotional well‐being, social functioning, anxiety, fatigue, sexuality (Mishra et al., 2012), pain (Irwin et al., 2015), cardiac disease risk, bone health (Kirkham, Bland, Sayyari, Campbell, & Davis, 2016) and possibly cognitive function (Campbell et al., 2017; Myers, Koleck, Sereika, Conley, & Bender, 2017). Additional exercise benefits for breast cancer survivors may include improved longevity. Specifically, associations have been observed between levels of exercise and cancer recurrence, new primary cancers, cancer‐related mortality and all‐cause mortality, with decreased rates of 28%, 21%, 33% and 46% respectively (Dieli‐Conwright, Lee, & Kiwata, 2016). To potentially achieve these exercise benefits, the American Cancer Society recommends that cancer survivors engage in a minimum of 150 weekly minutes of moderate‐intensity exercise (Rock et al., 2012). However, only from 17% (Smith & Chagpar, 2010) to 37% (Blanchard, Courneya, & Stein, 2008) of breast cancer survivors adhere to these recommendations. Interventions are needed to increase these exercise levels and potentially improve the quality and duration of breast cancer survivorship.

## BACKGROUND

2

Interventions that focus on exercise outcome expectations (OEs) may be useful in increasing exercise levels among breast cancer survivors. OEs refer to what people expect to obtain or avoid by engaging in a behaviour (Bandura, 2004). People exercise because they believe that it will produce desired and mitigate undesired outcomes. According to several prominent health behaviour change theories, high OEs lead to behaviour change (Ajzen, 1991; Bandura, 2004; Prochaska, Redding, & Evers, 2002). Among non‐cancer populations, individuals who expect more positive and less negative outcomes of exercise have stronger intentions to exercise and tend to exercise more (Brassington, Atienza, Perczek, DiLorenzo, & King, 2002; Schutzer & Graves, 2004).

Little is known about how OEs influence exercise among breast cancer survivors. Two studies that helped increase exercise among breast cancer survivors manipulated OEs by emailing participants “realistic expectations of exercise” (Hatchett, Hallam, & Ford, 2013) and “addressing” OEs during counselling sessions. This suggests that targeting OEs is effective for this group. However, these previous interventions targeted several constructs at once; thus, the unique effects of OEs on exercise remain unknown. Furthermore, no interventions have targeted all the dimensions of OEs. Dimensions of OEs include: (i) importance—value placed on the outcome(s); (ii) certainty—perceived probability outcome(s) will occur; and (iii) accessibility—the frequency with which outcome(s) are considered (Gross, Holtz, & Miller, 1995; Olson, Roese, & Zanna, 1996; Petty & Krosnick, 2014). The first of these dimensions importance can be increased through elaboration of why outcomes are desirable, certainty can be increased by vicarious experience or the observation of another person obtaining outcomes and accessibility can be increased by implementing methods to prompt individuals to think about the association between exercise and its outcomes (Fazio, 1995; Wegener, Downing, & Krosnick, 1995). Vicarious experience can be achieved through narrative stories. Narratives are stories told in first person that connect the reader with the narrator and the narrator's experience (Bell & Bell, 2013). This connection results in the reader considering the information as more personally relevant, processing it more deeply and better retaining it (Hinyard & Kreuter, 2007). For example, as an active breast cancer survivor elaborates on outcomes personally experienced from exercise, the inactive breast cancer survivor becomes more certain that she, too, will experience similar outcomes if she exercises (Gross et al., 1995; Hinyard & Kreuter, 2007; Hopfer, 2012; Kreuter & Wray, 2003; Kreuter et al., 2008; Shaffer & Zikmund‐Fisher, 2013; Wegener et al., 1995). The physically active survivor is able to provide practical knowing (i.e. the knowledge that comes from doing what is proposed), derived from participatory action research (Heron & Reason, 1997, 2008). Previous research suggests that breast cancer survivors are influenced to act on messages received from other breast cancer survivors (Hopfer, 2012).

Breast cancer survivors often do not recognize the potential of exercise to help manage late and long‐term effects (Hirschey, Docherty, Pan, & Lipkus, 2016). They have low OEs of exercise having an impact on recurrence and mortality risk (Karvinen & Vallance, 2015). In one study, only 30% of survivors said that they thought exercise may decrease recurrence risk (Hirschey, Docherty, et al., 2016). However, survivors are typically motivated to change behaviours they believe will improve their long‐term outcomes and quality of life (O'Neill et al., 2013). Thus, increasing OEs may be effective to motivate exercise among breast cancer survivors.

The theoretical framework guiding this study (Figure 1) is adapted from Bandura's self‐efficacy theory (Bandura, 1982); the theory proposes that exercise increases when people both expect desired outcomes will occur (i.e. have high exercises OEs) (Bandura, 2004; Hatchett et al., 2013; Rogers et al., 2009, 2013) and believe that they can perform exercise (i.e. have high exercise self‐efficacy) (Bandura, 2004; Loprinzi & Cardinal, 2013). In contrast to the many studies targeted to increase self‐efficacy, tested strategies to increase OEs are few. Therefore, this study focuses on increasing OEs. This framework is novel because multiple OE dimensions are considered, importance, certainty and accessibility. Prior interventions have simply informed participants about exercise benefits, thereby failing to address multiple OE dimensions (Hatchett et al., 2013; Rogers et al., 2009; Short, James, Girgis, D'Souza, & Plotnikoff, 2014). Conversely, this study is designed to target and increase all three OE dimensions, which in unison are hypothesized to increase exercise intentions (the most proximal predictor of behaviour) (Ajzen, 1991; Scholz, Keller, & Perren, 2009) and exercise. This approach may be more successful than previous attempts to increase exercise OEs.

**Figure 1 nop2119-fig-0001:**
[figure not shown]
Theoretical framework

Successful exercise interventions often require numerous resources such as health coaches, exercise trainers and equipment. Subsequently, many of the best interventions are not translated into practice. Therefore, the exercise intervention designed and tested here, Moving On, instead relies on the distribution of exercise booklets, a low‐cost exercise intervention that can be implemented into clinic settings. Exercise intervention booklets have been shown to be effective (Hirschey, Lipkus, et al., 2016; Short et al., 2014) and are a preferred (Stull, Snyder, & Demark‐Wahnefried, 2007) delivery mode among cancer survivors.

The purpose of this study is to test the feasibility of Moving On as an exercise intervention that can be translated into practice if effective. Moving On is a theory‐based, at home exercise intervention co‐created with physically active breast cancer survivors who use exercise to manage long‐term and late treatment effects. The primary aim of this study is to explore feasibility of Moving On among breast cancer survivors. A secondary aim is to test intervention effects on OEs and exercise. The secondary aim tests two hypotheses: first, that OE importance, certainty and accessibility will increase more in the intervention compared to the attention control arm; second, that exercise will increase more in the OE arm than the attention control arm.

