#### Sample size

3.2.2

Power analyses for mixed models were performed using the optimal design to estimate detectable effect sizes. The analyses revealed that the required sample sizes for detecting a small (δ = 0.20), medium (δ = 0.50) and large (δ = 0.80) effect size of change in OE importance, certainty and accessibility, with a power of 0.80, at a significance level of α = 0.05, are 944, 154 and 62 respectively. Due to the exploratory nature of this study, 60 patients will be recruited. This sample size will allow for examination of the strength and direction of intervention effects.

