#### Intervention effects

3.3.2

Two‐level multilevel modelling will be done using Proc Mixed with SAS software version 9.4. In the level‐1 model, outcomes will be modelled as a linear function of time (baseline, 4‐, 8‐ and 12‐weeks postintervention) to create growth trends. In the level‐2 model, the growth trends will be modelled as a linear function of arm (intervention vs. control). Models will be constructed for OEs, exercise intentions, subjective exercise and objective exercise. For OEs, each dimension will be modelled individually to determine if intervention effects differed between OE dimensions and the average of all dimensions will also be modelled. The level of significance will be set at 0.05, two‐tailed. Effect sizes will be calculated by dividing each beta coefficient by the square route or residual error variance for each outcome. This value is interpreted similar to Cohen's d in which a small effect is 0.2, a medium effect is 0.5 and a large effect is 0.8 (Cohen, 1988).

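### Separate models for each outcome-expectation dimension cannot show whether the intervention effect differs between dimensions, which is their stated purpose

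*Protocol article*

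**What the plan says.** All references are to the Protocol article.

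- **Background, final paragraph.** Feasibility is the primary aim. The secondary aim tests two hypotheses, of which the first is "first, that OE importance, certainty and accessibility will increase more in the intervention compared to the attention control arm".
- **3.3.2 Intervention effects.** Outcomes are modelled as linear growth over four time points, with arm at the second level. The plan for the OE outcomes reads: "each dimension will be modelled individually to determine if intervention effects differed between OE dimensions and the average of all dimensions will also be modelled". On the threshold: "The level of significance will be set at 0.05", two-tailed. Each beta is divided by the square root of that outcome's residual variance to give an effect size.
- **3.2.2 Sample size.** "Power analyses for mixed models were performed using the optimal design to estimate detectable effect sizes". The required totals for small, medium and large effects, "with a power of 0.80, at a significance level of α = 0.05, are 944, 154 and 62 respectively". Sixty participants will be recruited because the study is exploratory.
- **Discussion.** The strength and direction of effects will be identified, and the information gained will be used to refine the booklet and procedures before a larger study.

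Section 3.3.2 therefore names a question (do effects differ between dimensions?) and the method meant to answer it (one model per dimension).

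**The concern.** The method does not answer the question. Each single-dimension model asks whether that dimension's arm effect differs from zero. Whether two arm effects differ from each other is a separate question, and it needs the standard error of their difference. The same women rate the same 20 possible outcomes on all three dimensions, so the estimates are correlated. The standard error of a difference depends on that correlation, which three separate fits never estimate.

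What remains is an informal comparison of p-values or effect sizes. With 60 participants, a mixture of significant and non-significant results is likely even when the booklet works equally well on every dimension. The booklet has separate importance, certainty and accessibility sections. A chance pattern such as certainty significant and accessibility not could lead the team to rework a section that was doing as well as the others.

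**Working it through.** **Inputs.** From the document: total N = 60 with equal allocation, four time points, two-tailed 0.05, standardised effects of 0.20, 0.50 and 0.80. Assumed: the same true effect in all three dimensions, and a common correlation r between the three dimensions' test statistics. The document does not give r, so 0 to 0.9 is shown. Because the same items are rated three times, r = 0 is an extreme case.

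**Step 1: reproduce the printed sample sizes.** The test is the linear-growth F test of arm on slope, with noncentrality N·δ²/[4(1 + V)] on 1 and N − 2 degrees of freedom. V = 1/Σ(t − t̄)² = 1/5 for four equally spaced times, assuming slope and residual variances are both 1.

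- δ = 0.20, N = 944: 944 × 0.04/4.8 = 7.87, power 0.800
- δ = 0.50, N = 154: 154 × 0.25/4.8 = 8.02, power 0.804
- δ = 0.80, N = 62: 62 × 0.64/4.8 = 8.27, power 0.808

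These are the smallest even totals reaching 0.80, so 944, 154 and 62 are reproduced exactly. The normal approximation with the same variance factor gives 942, 152 and 60. Splitting alpha three ways raises those to 1258, 202 and 80. The printed figures therefore fit one OE score tested at unadjusted 0.05.

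**Step 2: single-dimension power at N = 60.** For δ = 0.80 the noncentrality is 60 × 0.64/4.8 = 8.00 and power is 0.794.

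**Step 3: how often three equal effects look unequal.** Simulate three normal test statistics with common correlation r, each centred at 1.96 + z(0.794) and compared with 1.96. Then P(mixed) = P(at least one significant) − P(all three significant).

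| r | at least one | all three | mixed |
|---|---|---|---|
| 0 | 0.991 | 0.501 | 0.490 |
| 0.5 | 0.947 | 0.602 | 0.345 |
| 0.7 | 0.917 | 0.651 | 0.266 |
| 0.9 | 0.867 | 0.714 | 0.153 |

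Check at r = 0: 1 − 0.794³ − 0.206³ = 1 − 0.501 − 0.009 = 0.490.

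**Step 4: sensitivity, same subtraction.**

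- δ = 0.50, N = 60: 0.797 − 0.070 = 0.73 (r = 0); 0.663 − 0.176 = 0.49 (0.5); 0.602 − 0.232 = 0.37 (0.7); 0.519 − 0.309 = 0.21 (0.9).
- δ = 0.80 with about 50 retained (60 × 0.83, the attrition limit in 3.3.1): 0.977 − 0.367 = 0.61; 0.909 − 0.490 = 0.42; 0.867 − 0.546 = 0.32; 0.804 − 0.621 = 0.18, in the same order of r.

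**Step 5: what a direct contrast would deliver.** In the Step 1 units, one arm effect has standard error √(4.8/60) = 0.283. The difference between two has standard error 0.283 × √[2(1 − r)]. The 95% half-width is 1.96 times this: 0.78 (r = 0), 0.55 (0.5), 0.43 (0.7) and 0.25 (0.9). The answer depends strongly on r, which only a joint model estimates.

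**The case against.** The strongest reply has three parts.

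- **This is an exploratory question under a secondary aim of a feasibility trial.** True, and it limits the weight of the point. But the plan still sets a significance level and states that the models are to determine whether effects differ.
- **The plan never says it will compare p-values; it also plans an effect size for each outcome.** That is fair, and the mixed-significance figures show a risk of misreading rather than a declared rule. However, three effect sizes without a standard error for their differences do not settle whether they differ. Each is also scaled by its own residual variance, so two can differ because the residual variances do.
- **Such detail belongs in a full protocol or analysis plan.** Silence could be excused on that ground, but 3.3.2 is not silent: it pairs this purpose with this method.

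A stronger reading is tempting. A reader might infer that Hypothesis 1 needs all three dimensions significant, that its power at 60 is only 0.50 to 0.71 against a promised 0.80, and that the planned average score would repair this. The document does not support it.

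- Section 3.2.2 ties 0.80 to 944, 154 and 62, and claims no power at 60.
- No success rule is stated, whether all three, any one or the average. The remark that the dimensions act in unison concerns their joint influence on exercise intentions.
- The 0.50 to 0.71 range requires δ = 0.80 and r between 0 and 0.9. At δ = 0.50 it is 0.07 to 0.31.
- The average cannot show that all three rise. If only two rise by 0.80, it is still significant with probability 0.48 (r = 0.9) to 0.90 (r = 0).

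**Conclusion.** The point holds in a limited form. The analysis in 3.3.2 cannot deliver the between-dimension comparison that it is said to deliver. With equal true effects of 0.80 and 60 participants, significance would be mixed in about 49%, 35%, 27% or 15% of trials at r = 0, 0.5, 0.7 or 0.9. The proportion is higher for a medium effect or after attrition. These figures rest on equal effects, a common assumed correlation and the variance factor that reproduces the printed sample sizes. The logical point, that separate fits give no test or interval for a difference, needs none of these assumptions.

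The feasibility aim is unaffected and no power statement is shown to be false. As a secondary clarification, 944, 154 and 62 correspond to one OE score at unadjusted 0.05, although the sentence lists three dimensions.

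**What to change.** In 3.3.2:

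- Fit one joint mixed model of the three OE dimensions, on a common or standardised scale and allowing for correlation within person across dimensions and times.
- Examine whether effects differ through the arm-by-time-by-dimension interaction, with 95% confidence intervals for the between-dimension contrasts.
- Report the single-dimension models as estimates with 95% confidence intervals, and draw no conclusion about differences from which of them reach 0.05.

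In 3.2.2, add that the printed totals apply to a single OE score. If the authors want the average score to decide Hypothesis 1, that hypothesis must first be reworded to concern overall OE.

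The cost is one extra model and a few sentences, with no new data or participants. The interaction will have modest power at 60, so the contrasts may be wide and inconclusive, but they would show openly how little can be said about differences.

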## THE STUDY

3

### Design

3.1

This feasibility study is a randomized two‐arm trial. Eligible participants will provide written, informed consent and be given a Fitbit^®^ to wear for 2 weeks to establish baseline activity level. At baseline, they will also complete online questionnaires assessing OEs, self‐efficacy and exercise. Participants will receive an intervention or control booklet via mail and will have 1 week to complete it. Follow‐up measures will be collected at 4‐, 8‐ and 12‐week postintervention using the Fitbit^®^ and online questionnaires.

### Method

3.2

#### Participants and setting

3.2.1

Participants will be recruited at a tertiary cancer centre in the Southeastern United States. Inclusion criteria will include: (i) stage IA–IIB breast cancer diagnosis; (ii) 2 months–10 years status postsurgery, radiation and chemotherapy; (iii) ability to read and write English; (iv) no evidence of recurrence; (v) being inactive (self‐reported ≤150 min/wk moderate–strenuous‐intensity exercise); (vi) no contraindications to exercise based on the Physical Activity Readiness Questionnaire (PAR‐Q) (Thomas, Reading, & Shephard, 1992); (vii) approval for participation by an oncologic provider; (viii) access and ability to use a computer for completion of online measures; and (ix) possession of a smartphone for the Fitbit^®^ to be synced to.

#### Sample size

3.2.2

Power analyses for mixed models were performed using the optimal design to estimate detectable effect sizes. The analyses revealed that the required sample sizes for detecting a small (δ = 0.20), medium (δ = 0.50) and large (δ = 0.80) effect size of change in OE importance, certainty and accessibility, with a power of 0.80, at a significance level of α = 0.05, are 944, 154 and 62 respectively. Due to the exploratory nature of this study, 60 patients will be recruited. This sample size will allow for examination of the strength and direction of intervention effects.

#### Random assignment

3.2.3

Participants will be randomized with equal probability to the attention control or intervention arm. A blinded research assistant will orient patients to the study and facilitate data collection. To reduce performance bias among participants, the study will be introduced as being about important lifestyle information. Participants will be told that they will receive diet and exercise information and be randomly assigned to a group focused more on exercise or more on diet.

#### Intervention

3.2.4

The intervention, Moving On, consists of an exercise OE booklet containing narrative messages, writing and thinking activities intended to increase OE dimensions of importance, certainty and accessibility. The booklet provides a global overview of the many and diverse positive outcomes breast cancer survivors may experience from exercise. The booklet cover (Figure 2a) contains the study name, Moving On. This name captures the stage of cancer survivorship and encourages participants to take action by moving, that is, exercising. The cover image was selected because the research team thought it was uplifting and motivational. The woman in the picture is intended to be relatable to many breast cancer survivors because she is of average to slightly above average weight, and her age and race are ambiguous. The first page of the booklet (Figure 2b) introduces the ACS recommendations on diet and exercise for cancer survivors. The second page (Figure 2c) lists outcomes associated with exercise for breast cancer survivors (e.g. decreased fatigue, improved survival). This section aims to increase awareness of the many benefits of exercise for breast cancer survivors. It explicitly states that because one has had breast cancer and treatment, these outcomes may be especially important. To increase OE importance, there is a section (Figure 2h) instructing the participant to select the three outcomes that she would most like to experience from exercise and then elaborate on all the things that will happen if those outcomes occur. OE certainty is primarily targeted in the intervention through three narrative messages, two from breast cancer survivors who exercise regularly and one from an oncologist (Figures 2d–2f). Each survivor narrative is a few long paragraphs, written in first person and includes a photograph of the author. The survivors’ narratives summarize the women's personal stories of: (i) cancer treatments and side effects they experience; and (ii) outcomes obtained as a result of exercise and how achieving these outcomes helped them manage symptoms (e.g. stress, pain). The oncologist's narrative contains: (i) her personal recommendation for breast cancer survivors to exercise; and (ii) outcomes she believes survivors may obtain, based upon current research. Finally, to increase OE accessibility, the booklet instructs participants to identify at least three strategies that could motivate them to think about outcomes they may experience if they exercise regularly (Figure 2g). Suggestions (e.g. reading booklet daily, making a computer screen saver) are provided.
